## Abstract

**Background:**

Ultrasound-guided transversus abdominis plane block (TAP) performed by anesthesiologist has been shown to be an effective and safe analgesia method in abdominal surgery, reducing postoperative opioid consumption. Recently, there has been growing interest to insert TAP under laparoscopic vision (LTAP) by surgeon. LTAP has been used in laparoscopic gastrointestinal surgery, but studies on LTAP in gynecologic laparoscopic surgery are sparse and inconsistent. The purpose of this study is to compare the efficacy of LTAP and local wound analgesia in laparoscopic surgery due to suspected or diagnosed superficial peritoneal endometriosis.

**Methods:**

The LTAP-trial is a prospective randomized controlled double-blinded study comparing the efficacy and safety of LTAP with local wound analgesia in laparoscopic endometriosis surgery. Patients are randomized to receive LTAP with levobupivacaine and wound infiltration with placebo or wound infiltration with levobupivacaine and LTAP with placebo. The primary outcome is postoperative opioid consumption measured by patient-controlled analgesia (PCA) pump. Secondly, subjective postoperative pain up to 24 h postoperatively will be measured by Numeric Rating Scale (NRS). Additional outcome measures are factors related to recovery and length of stay in the hospital as well as a 6-month follow-up survey regarding pain (NRS) and endometriosis-related wellbeing (endometriosis-related health profile, EHP-30) after surgery. A total of 46 patients will be randomized in a proportion of 1:1.

**Discussion:**

Patients with peritoneal endometriosis are often prone to severe postoperative pain that may prohibit their enhanced recovery after laparoscopy. Thus, there is a need for effective postoperative pain management with minimal side-effects. This study focusing on laparoscopically inserted transversus abdominis plane block may provide new insight in dealing with postoperative pain after laparoscopic endometriosis surgery as well as after other gynecologic surgery.

**Trial registration:**

The LTAP-trial -protocol has been prospectively registered to ClinicalTrials.gov, ID: NCT04735770. Registered on February 2021.

## Administrative information

Note: the numbers in curly brackets in this protocol refer to SPIRIT checklist item numbers. The order of the items has been modified to group similar items (see http://www.equator-network.org/reporting-guidelines/spirit-2013-statement-defining-standard-protocol-items-for-clinical-trials/).

## Introduction

### Background and rationale {6a}

Endometriosis is a chronic disease affecting about 10% of women during their fertile years. Patients often suffer from chronic pelvic pain that decreases markedly their quality of life. Conservative hormonal medication, being the primary treatment option, is often insufficient due to persisting pain, contraindications, or side-effects such as irregular bleeding. Hence, there is also need for surgical treatment of peritoneal endometriosis [1]. Clinical observations have shown that patients with endometriosis tend to suffer from more severe postoperative pain after pelvic surgery than other patients [2]. This may be due to hypersensitization of sensory pelvic nerves, which is caused by the inflammatory nature of endometriosis. Dysmenorrhea, which is the leading symptom of endometriosis, is a prognostic factor for the severity of postoperative pain [3]. The use of epidural or local wound analgesia after endometriosis surgery has been common practice. However, local wound analgesia is often insufficient for endometriosis patients, who tend to suffer from more severe postoperative pain [2]. Epidural analgesia carries a risk of potentially harmful complications and may also prohibit enhanced recovery after surgery (ERAS) and prolong time to discharge. In addition, postoperative opioid consumption also predisposes to complications such as nausea, vomiting, and respiratory depression.

Dorsally inserted transversus abdominis plane block (TAP) has been used as a part of multimodal analgesia in abdominal surgery since the beginning of twenty-first century [4]. TAP blocks the sensory nerves of the abdominal wall unilaterally between the costal margin and the inguinal ligament (T6–L1), and it provides analgesia to the parietal peritoneum, muscles, and abdominal skin accordingly [5]. When inserted in a blind fashion, it carries a risk of visceral injury. To avoid complications, ultrasound-guided transversus abdominis plane block technique (UTAP) was adopted by anesthesiologists. Both methods have been shown to serve as an effective postoperative analgesia reducing postoperative opioid consumption and opioid-related side effects after open and laparoscopic abdominal surgery [6].

Laparoscopically inserted transversus abdominis plane block (LTAP) is a novel technique that has been used by gastrointestinal surgeons, especially in laparoscopic cholecystectomies and colorectal surgery [7, 8] with equally good results in comparison to UTAP [9]. According to a recent meta-analysis, LTAP is safe and superior to local wound analgesia in adults undergoing minimally invasive surgery (such as laparoscopic or robotic abdominal procedures) regarding early pain control, opioid consumption, and patient satisfaction [10]. In another study, a reduction in postoperative pain score measured by visual analog scale was noted even at 1 week after laparoscopic cholecystectomy with LTAP in comparison to local wound analgesia [11]. LTAP has been suggested to reduce postoperative pain and opioid need in gynecologic and endometriosis laparoscopic surgery, but the results of previously published studies have been inconsistent [12–14]. The purpose of this study is to investigate whether LTAP provides a post-laparoscopic opioid-sparing effect in comparison to local wound analgesia, thus diminishing opioid related side-effects and improving ERAS.

### Objectives {7}

The objective of this prospective, randomized, controlled, double-blinded study is to examine whether LTAP is superior, i.e., reduces the postoperative opioid consumption compared to local wound analgesia in treating post-laparoscopic pain in patients suffering from pelvic pain because of suspected endometriosis.

## Methods/design

### Trial design {8}

This is a prospective, randomized, controlled, double-blinded clinical study evaluating the effectiveness and safety of LTAP compared to local wound analgesia in laparoscopic gynecological surgery for superficial peritoneal endometriosis. Randomization at patient level is done with an allocation ratio of 1:1. The active LTAP group will receive a long-acting local anesthetic, levobupivacaine, administered at LTAP points and saline infiltrated at the sites of laparoscopic ports. The control group will receive saline at LTAP points and levobupivacaine at the sites of laparoscopic ports. The patient and the surgeon remain blinded to the allocated group until the end of the study data collection.

The aim of this study is to explore whether LTAP is superior, i.e., offers opioid-sparing effect when compared to local wound analgesia in postoperative pain after laparoscopic gynecological surgery for peritoneal endometriosis. The power calculation for this study was based on 50% reduction in the consumption of opioids during the postoperative period, which we estimated to be clinically relevant. The study protocol flow chart and time of collection of outcomes are described in Figs. 1 and 2, respectively.

**Fig. 1 Fig1:**
[figure not shown]
Flow chart describing the study protocol

**Fig. 2 Fig2:**
[figure not shown]
Time of collection of outcomes

### Study setting {9}

This is a single-center trial located in a tertiary university hospital in Finland.

### Eligibility criteria {10}

The inclusion criteria are as follows:
Age 18–50 yearsDiagnosed or suspected peritoneal endometriosis and laparoscopic surgery indicatedASA 1–3

The exclusion criteria:
Sleep apneaASA > 3Contraindications to opioids or non-steroidal anti-inflammatory drugsContinuous opioid intake preoperatively

The laparoscopies and LTAP administration will be performed by two experienced laparoscopists, who work within a multi-professional team focusing on endometriosis surgery in a tertiary hospital setting.

### Who will take informed consent? {26a}

Informed consent will be obtained during the preoperative clinical review at the outpatient clinic by the operating gynecologist.

### Additional consent provisions for collection and use of participant data and biological specimens {26b}

Not applicable. No biological specimens will be collected.

## Interventions

### Explanation for the choice of comparators {6b}

Local wound infiltration with levobupivacaine has been the most commonly used mode of postoperative analgesia in laparoscopic surgery in our clinic. To explore the possibilities of improving the efficacy of postoperative pain management after peritoneal endometriosis surgery, we decided to choose LTAP with levobupivacaine as a comparator. Administration of LTAP has a fast learning curve and it does not increase the operative time markedly.

### Intervention description {11a}

#### Outpatient clinic

After giving informed consent, study participants will fill in preoperative validated questionnaires regarding pain (Numeric Rating Scale, NRS) and endometriosis-related health (Endometriosis Health Profile, EHP-30).

#### Operating room; anesthesia

Total intravenous anesthesia will be administered to both groups in a standardized fashion using propofole and remifentanil infusions. No inhalation anesthetics will be used. Dexamethasone 5 mg iv will be administered for the prevention of postoperative nausea and vomiting (PONV).

#### Operating room; interventional treatment

Operating room (OR) nurse will randomize participants to intervention or control group with an allocation ratio of 1:1 by fetching a sealed opaque numbered envelope from the office of the operating ward. The envelope will be opened and sealed again and the levobupivacaine and saline will be prepared in identical looking syringes according to allocation before the operating surgeon enters the OR. The LTAP and local wound analgesia will both be administered at the beginning of the operation under laparoscopic vision by the surgeon. LTAP will be infiltrated bilaterally at the upper and lower quadrants between front axillary and mid-clavicular lines in the depth reaching the space between transverse abdominal and internal oblique muscles. Local wound infiltration will be administered to all trocar sites prior to incision. The study group will be given LTAP with 20 ml levobupivacaine 2.5 mg/ml bilaterally and local wound infiltration with saline 10 ml in total as placebo. The control group will be administered with saline 20 ml bilaterally as placebo to the sites corresponding LTAP and local wound infiltration with levobupivacaine 5 mg/ml 10 ml in total.

#### Operating room; surgical technique

Standard surgical care according to our protocol in laparoscopic surgery of suspected peritoneal endometriosis will be given. Peritoneal endometriosis implants will be resected using a monopolar hook. Bipolar energy instrument may be used to ensure hemostasis where needed.

#### Postoperative analgesia

At the end of the procedure, 50 mg of dexketoprofen iv and fentanyl 0.5 μg/kg iv will be administered as remifentanil infusion is discontinued. As the patient arrives in the recovery room, a PCA pump (Delta Legacy iv) will be started with oxycodone 3 mg/ml with 1.5 mg boluses maximum of 4 per hour. Iv oxycodone may be administered in addition to the PCA-pump as a rescue analgesia. Paracetamol 1 g × 3 po and ibuprofen 600 mg × 3 po are started. Early mobilization and other ERAS protocols will be implemented.

### Criteria for discontinuing or modifying allocated interventions {11b}

Not applicable. Allocation and allocated intervention are done minutes apart on anesthetized patients, so no need for modification is expected.

### Strategies to improve adherence to interventions {11c}

The preoperative data as well as the outcome measure data during the hospital stay will be collected by the hospital staff. The study participants that have not returned the 6-month questionnaires will be contacted by the investigators to improve the response rate using their contact details (address, phone number) that can routinely be found in the clinical patient notes in Finland.

### Relevant concomitant care permitted or prohibited during the trial {11d}

Treatment of the patient will be conducted by standard care protocols regardless of the trial participation.

### Provisions for post-trial care {30}

Ancillary and post-trial care including the care of possible complications will be given according to standard medical practice irrespective to the trial itself. Every patient receiving medical or surgical care in Finland is covered by the Finnish Patient Insurance Centre. Possible complications caused by the study interventions are compensated via the center.

### Outcomes {12}

Primary outcome is the overall 24 h postoperative opioid consumption compared between the study groups. The amount of oxycodone administered via the PCA-pump and possible rescue analgesics (oxycodone administered in addition to the PCA-pump) will be converted to morphine equivalents.

As secondary outcomes, the following will be measured:
Postoperative pain using NRS scaled from 0 to 10 (0 meaning no pain and 10 meaning “worst imaginable pain”). The maximum experienced pain will be recorded at the recovery room. Additional NRS will be recorded at the ward every six hours up to 24 h (if the patient is discharged before 24 h, they are requested to fill in the NRS at home).Factors related to ERAS (nausea, vomiting, peroral intake, mobilization, complications, time of discharge, readmission to hospital) will serve as other outcomes and will be documented and analyzed accordingly.A 6-month postoperative follow-up will be conducted using NRS pain inquiry and EHP-30 questionnaire being sent to participants.

### Participant timeline {13}

### Sample size {14}

Sample size was calculated based on the assumption that LTAP would decrease the postoperative opioid consumption by 50%, which was thought to be a clinically relevant difference. The calculation was based on previous literature showing a 15.4 mg ± 9.2 postoperative opioid consumption after local wound analgesia [15]. With 80% power and 0.05 alpha error, the sample size of 46 (23 + 23) was obtained to detect a decrease of 7.7 mg in opioid consumption from 15.4 mg in the control group to 7.7 mg in the intervention group, assuming a standard deviation of 9.2 mg. Sample size was calculated according to Chow et al. [16], and the calculation was performed with statistical program R.

### Recruitment {15}

All eligible patients referred to gynecological outpatient clinic at the Oulu University Hospital with diagnosed or suspected peritoneal endometriosis needing laparoscopic evaluation or surgery because of insufficient response to medical management will be considered as potential trial participants. After receiving thorough information on the study protocol including possible advantages and disadvantages, and after voluntary signing of the informed consent, the trial participants will be enrolled to the LTAP-trial.

## Assignment of interventions: allocation

### Sequence generation {16a}

A computer-created random allocation list with simple randomization will be created and numbered; sealed opaque letters will be done to confirm blinding. The list will be created by the study statistician and the envelopes by the study nurse who are not involved in data collection or patient care.

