## Statistical methods

### Statistical methods for primary and secondary outcomes {20a}

Statistical analyses will be performed on an intention-to-treat basis using IBM SPSS software by the study statistician who does not participate in patient care or data collection. Continuous variables will be described as mean with standard deviation (SD) or as median with 25th–75th percentiles and categorical variables as numbers and percentage of proportions. Comparison between the study groups will be conducted using the Student’s *t*-test or Welch test for continuous variables, Mann-Whitney *U* test for variables measured at ordinal scale, and the chi-square or Fisher’s test for categorical variables. Furthermore, continuous variables with measurements both pre- and postoperatively will be analyzed using linear regression model with preoperative measurement as an adjusting factor. The statistical significance limit is set at two-sided *p*-value < 0.05.

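### Simple randomization of 46 patients leaves near-equal arms, and balance across the two surgeons, to chance; blocking within surgeon is a cheap, minor improvement

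*Protocol article*

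**What the plan says.** The allocation method is fixed under Sequence generation {16a}: "A computer-created random allocation list with simple randomization will be created and numbered". The protocol describes no blocks, strata, minimization or other restriction. The allocation ratio is given as 1:1 in the abstract, under Trial design {8} and in the description of the interventional treatment.

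The planned arm sizes are under Sample size {14}: "With 80% power and 0.05 alpha error, the sample size of 46 (23 + 23) was obtained". The inputs there are a fall from 15.4 mg to 7.7 mg, "assuming a standard deviation of 9.2 mg".

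On operators, Eligibility criteria {10} says: "The laparoscopies and LTAP administration will be performed by two experienced laparoscopists". Surgeon does not appear in the allocation. It does not appear in the group comparison under Statistical methods {20a} either, which for continuous outcomes is a Student or Welch test.

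**The concern.** With a few dozen patients, an unrestricted list can give visibly unequal arms, and unequal arms cost some power at a fixed total. The same list can also place one surgeon's cases more in one arm than in the other. Here the operator both delivers the block and performs the surgery, so surgeon is the obvious factor to balance, and it has only two levels. Recruitment was planned from April 2021 to the end of 2022, and an unrestricted list does not hold the arms level over that period.

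At stake are a small amount of power and the ease of reading the result if the arms differ visibly in size or in surgeon. The validity of the comparison is not at stake.

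**Working it through.** **Inputs.** From Sample size {14}: difference 7.7 mg, common SD 9.2 mg, power 80%, alpha 0.05, total 46. From Statistical methods {20a}: two-sided testing and a t-test. From Sequence generation {16a}: simple randomization, so each patient goes to either arm with probability 0.5.

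**Step 1: reproduce the plan's figure.** By the normal approximation, n per arm = 2 × (1.960 + 0.842)² × (9.2/7.7)² = 22.41, rounded up to 23, total 46. This matches the protocol. Power at 23 + 23 is 81.0% by that approximation and 79.3% by the noncentral t distribution, which corresponds to the planned Student test.

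**Step 2: distribution of arm sizes.** The size of one arm is Binomial(46, 0.5). The chance of exactly 23/23 is C(46, 23)/2⁴⁶ = 11.7%.

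**Step 3: power at each split.** For arms n₁ and n₂ the noncentrality is 7.7 / (9.2 × √(1/n₁ + 1/n₂)), with 44 degrees of freedom. At 23/23 this is 7.7/(9.2 × 0.2949) = 2.84. At 18/28 it is 7.7/(9.2 × 0.3021) = 2.77. At 16/30 it is 7.7/(9.2 × 0.3096) = 2.70.

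| Split | Power, t-test | Power, normal approximation | Chance of a split this uneven or worse |
|---|---|---|---|
| 23/23 | 79.3% | 81.0% | 100% |
| 20/26 | 78.6% | 80.4% | 46.1% |
| 19/27 | 78.0% | 79.8% | 30.2% |
| 18/28 | 77.3% | 79.1% | 18.4% |
| 17/29 | 76.4% | 78.2% | 10.4% |
| 16/30 | 75.3% | 77.2% | 5.4% |
| 15/31 | 74.0% | 75.8% | 2.6% |

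**Step 4: average over all lists.** Weighting each split's power by its binomial probability gives 78.4% (t-test) or 80.1% (normal approximation). The mean cost of simple randomization is therefore 79.3 − 78.4 = 0.9 point (t-test), or 81.0 − 80.1 = 0.9 point (normal approximation).

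**Step 5: surgeon balance.** The document gives no caseload per surgeon, so the split is an assumption. The chance that the two arms differ by at least 20 percentage points in one surgeon's share is about 19% if the cases divide 23/23 between surgeons, 15% if 15/31 and 11% if 10/36. These are chances of imbalance only. Without a surgeon effect they cannot be turned into an effect on the result.

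**Step 6: after the fix.** Blocks within two surgeon strata do not force exactly 23/23, because each stratum can stop in mid-block. With blocks of at most 4, each stratum can be out by 2, so the worst overall split is 21/25, with t-test power 79.0%. With blocks of at most 6, each can be out by 3, so the worst is 20/26, with 78.6%.

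**The case against.** The strongest reply is that almost nothing is lost. About 70% of lists (100 − 30.2) are 20/26 or closer, where the loss is at most 79.3 − 78.6 = 0.7 point. Simple randomization is unbiased for surgeon and calendar time, and the p-value already allows for chance imbalance. Both surgeons are described as experienced and work in one team at one centre. This stands, and it is why the point is minor.

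A reader might infer more from the same facts. The document does not support these readings:

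- **That 1:1 allocation is not delivered.** The ratio is a probability of one half per patient, which simple randomization gives. Only equal realised arm sizes are not assured.
- **That the 80% power depends on an exact 23/23 split, or that 46 is wrong.** The figure reproduces. The 11.7% chance of an exact split looks alarming but matters little, because near-equal splits cost almost nothing. The gap between 81.0% and 79.3% is the normal approximation against the t distribution, and blocking would not remove it.
- **That unequal variances in unequal arms are unhandled.** Statistical methods {20a} allows the Welch test.
- **That missing primary data make this worse.** The document gives no rate of missing data and plans multiple imputation. Any such loss is also a separate matter from the allocation method.

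Blocking has its own usual objection, predictability. That is weak here. The envelopes are opaque and sequentially numbered, nurses open them in the operating room, and the surgeons who enrol are blinded.

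**Conclusion.** The point holds as a minor design weakness with an inexpensive remedy. The allocation method leaves to chance an arm balance and a surgeon balance that could be had with no increase in sample size.

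The mean cost is about 0.9 point of power. In roughly one list in five (18.4%) the loss is 2 points or more (79.3 − 77.3), and in about one in twenty (5.4%) it is 4 points or more (79.3 − 75.3). These figures assume the protocol's own difference and SD, equal variances, all 46 patients analysed, and a two-sided t-test at 0.05.

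The harm from surgeon imbalance cannot be quantified from this document.

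**What to change.** Under Sequence generation {16a}, replace simple randomization with permuted blocks of randomly varying size, stratified by operating surgeon. The statistician generates the list as now, and the sequentially numbered opaque envelopes are kept, with one series per surgeon. Block sizes should not be disclosed to clinical staff.

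Under Statistical methods {20a}, include surgeon as a factor in the primary comparison, for example in a linear model with treatment arm and surgeon. Otherwise any precision gained by stratifying is not used. If the protection of the Welch test is to be kept, use a standard error that allows unequal variances.

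The sample size section needs no change on this account.

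The cost is a new list, new envelopes, a short amendment, and two series to manage so that the right one is drawn for the operating surgeon. There is slight predictability at block ends, visible mainly to the nurses who open the envelopes. They do not enrol patients, so the risk of selection is small. If recruitment has begun, only the unopened envelopes can be blocked. If it is complete, only the surgeon factor remains available, and it should be fixed before unblinding.
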